
#### **6.4. *Interim analysis and interruption criteria***

The study withdrawal criteria will be:

- The presence of serious adverse events that lead patients to stop taking the product.
- The appearance of a serious disease with hospitalisation criteria.
- The taking of drugs other than those described as permitted.
- Non-compliance with the diet, defined by the following criteria:
  - energy provided by lipids more than 40%.
  - energy provided by saturated fatty acids higher than 15%.
- Non-compliance with fibre treatment. Compliance below 80% will be grounds for withdrawal.

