## 7. DESCRIPTION OF THE TREATMENT

### 7.1. *Treatment regimens*

During the initial treatment period (8 weeks) the patients will be given either the treatment with *Plantago ovata* husk (Plantaben) or placebo, according to the randomisation group.

The dose will be 20 g p.o. daily in the form of effervescent powder. This is the usual dose of the product in clinical practice.

The product will be distributed into 4 doses of 5 g, taken at main meal times, taking one dose at breakfast time, another at lunchtime and two with the evening meal.

The dose of fibre contained in Plantaben will total 14 g/d.

The duration of the treatment with each product will be 8 weeks. Subsequently, patients that do not fulfil the therapeutic objective will be given an added statin for a further 8 weeks. Patients who reach the therapeutic objective in the first 8 weeks will end follow-up at this time.

The statin chosen is Simvastatin 20 mg/day.

The fibre will be given at least 15 minutes before breakfast, lunch and the evening meal. The contents of the sachet should be dissolved in 200 – 250 ml of water and taken immediately.

The Simvastatin will be taken at night, 2 hours after the evening meal.

If the patient is regularly taking another medication, the time he/she takes it should be checked in order to avoid interference with the taking of the fibre and the statin or both.

If the regular medication is taken in the morning, it will be taken 2 h after breakfast to simulate the situation of fasting. In all cases, the medication should be taken 2 h after the meal.

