### 7.2. *Concomitant treatments*

#### 7.2.1. Permitted treatments

- . Diuretics
- . Beta-blockers
- . Calcium channel inhibitors
- . Angiotensin-converting enzyme inhibitors (ACEI).
- . Angiotensin II receptor antagonists (AIIRA).

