### 7.2.2 Prohibited treatments

- Statins (during the first 8-week period)
- Resins
- Fibrates
- Nicotinic acid and derivatives
- Ezetimibe
- Anticoagulants
- Minerals and vitamins
- Digoxin

It should be emphasised that patients may have followed some of the prohibited treatments for up to a minimum period of two months before their inclusion in the study.

All the drugs that the volunteer may take must be recorded.

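### Section 6.4 makes any drug outside five permitted antihypertensive classes a ground for withdrawal, while 7.1 and 7.2.2 leave a drug on neither list in use or not prohibited; each drug needs one status, and the S7 lipid pair should be kept

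*Protocol*

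**What the plan says.** Section 6.4 opens its list with "The study withdrawal criteria will be", and one bullet reads "The taking of drugs other than those described as permitted".

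The drugs described as permitted are in 7.2.1: diuretics, beta-blockers, calcium antagonists, ACE inhibitors and angiotensin II antagonists. There is no further category.

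Section 7.2.2 has its own list of eight prohibited entries, from lipid-lowering agents to anticoagulants, vitamins and minerals, and digoxin. It closes with "All the drugs that the volunteer may take must be recorded".

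Section 7.1 says "If the patient is regularly taking another medication, the time he/she takes it should be checked in order to avoid interference" with the fibre or the statin, and then spaces that medication from meals. No drug class is named. Visit S8 in 8.2 again goes over how the patient's regular medication is to be taken.

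Exclusion 9 in 6.2 rules out medications that may affect lipid metabolism or blood pressure.

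The primary comparison (12.3.1) is the S8 minus S0 change in LDL-C. Annex 1 places the post-baseline lipid profiles at S7 (two draws) and S15 (two draws) only. Section 12.4 defines intention to treat as analysis in the assigned group regardless of compliance, and a per-protocol set of suitable compliers.

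**The concern.** The withdrawal rule is keyed to absence from the permitted list, while the treatment section also works with a prohibited list. The two lists together do not cover all drugs, and for the remainder the sections point in different directions. A site working from 6.4 would withdraw a patient whom a site working from 7.1 and 7.2.2 would keep.

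What is at stake is the primary outcome. There is no lipid measurement between baseline and S7, and no sample is described for a patient who has been withdrawn. If withdrawal comes before S7, the patient belongs to the intention-to-treat group but has no S8 value to contribute. That loss would depend partly on how each site reads the protocol.

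**Working it through.** **Status of a drug under each section**

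- *In a 7.2.1 class (say, a beta-blocker).* 6.4: no withdrawal. 7.2.2: not prohibited. 7.1: timed and continued. Exclusion 9, however, would keep out a patient on a medication that may affect blood pressure, although 7.2.1 permits these classes and section 6 counts high blood pressure as a qualifying risk factor.
- *On the 7.2.2 list (say, a fibrate).* 6.4: withdrawal. 7.2.2: prohibited. The sections agree.
- *On neither list (say, a regularly taken analgesic).* 6.4: withdrawal. 7.2.2: not prohibited. 7.1 and S8: timed and, by implication, continued. The sections disagree.

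Read literally, 6.4 already catches every prohibited drug, so the 7.2.2 list would add nothing during the study beyond its use at entry. The two sections therefore look as if they were written to different rules.

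**The plan's own sample size**

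Inputs from 6.3: difference 7.5 mg/dl, SD 20 mg/dl, power 80%, alpha 0.05 (two-sided per 12.3.1), 1:1 allocation (5.2).

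n per group = 2 × (1.960 + 0.842)² × 20² / 7.5² = 2 × 7.85 × 400 / 56.25 ≈ 111.6, rounded up to **112**. The stated figure reproduces.

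**Margin in the fibre phase**

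The final sample is 145 per group, set by the second phase. With the planned 15% losses, 145 × 0.85 = 123.25 remain, which gives power of about 84%.

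The group falls below 112 when:

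- losses are added to the 15%: (123.25 − 112) / 145 = 7.8 percentage points, that is total losses of 33/145 = 22.8%;
- losses are applied to those remaining: 1 − 112/123.25 = 9.1%.

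So the planned 112 is missed at about 8 to 9% extra losses.

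**Illustration, losses added to the 15%**

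| Extra losses | Evaluable per group | Power |
|---|---|---|
| 0% | 123 | 83.7% |
| 5% | 116 | 81.5% |
| 10% | 109 | 79.0% |
| 20% | 94 | 73.0% |

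The extra-loss rates are assumptions. The protocol gives no rate of use of unlisted drugs, and 6.3 does not say which causes its 15% covers.

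**The case against.** The strongest reply is that 6.4 is a clear rule on its own: a closed permitted list, with anything else leading to withdrawal. On that view "All the drugs that the volunteer may take must be recorded" and the checks of concomitant treatment at S4 to S16 are simply how a site detects a breach. This is right as far as it goes: recording is not permission, so those instructions do not show that such patients stay in. The contradiction rests on 7.1 and S8, and on the existence of a separate prohibited list. Section 7.1 could be read as meaning only the permitted antihypertensives, but it does not say so. It also concerns regular medication, so it is silent on a single dose of an incidental drug.

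It is also fair that no section says a withdrawn patient must not be sampled, and that handling of missing S8 values may be left to the SAP. The lost outcome is an inference from the schedule. But an SAP cannot restore a measurement that was not taken.

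Two further readings are tempting and are not supported:

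- A reader might infer that 6.4 also catches the study simvastatin, which is not in 7.2.1. It is assigned treatment under 7.1 and S8, and 7.2.2 bars statins only in the first 8 weeks.
- A reader might infer that fibre patients would be withdrawn more often because they take remedies for bloating. Section 4.1 does expect flatulence and distension, but says that they resolve within days, and nothing in the protocol describes use of remedies by arm.

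Finally, the power figures use an unadjusted comparison. The planned baseline-adjusted ANCOVA would do somewhat better to the extent that baseline LDL-C explains the change.

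**Conclusion.** The sections contradict each other on drugs that are on neither list, and exclusion 9 conflicts with 7.2.1 on antihypertensives. Followed as written, 6.4 can remove a patient before the only draws that supply the primary outcome, which works against the as-assigned analysis in 12.4.

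The size is unknown. A reader might take the table as a forecast that the trial will be underpowered; the documents do not support that. It shows only that the fibre phase has room for about 8 to 9% losses beyond 15%, under three assumptions: that the rates shown occur, that they are not already inside the 15%, and that patients withdrawn before S7 are not sampled. Nor do the documents establish that the withdrawal rule itself is clinically wrong. The finding is that it is inconsistent with other sections and that its effect on outcome data is not addressed.

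**What to change.** 1. Reconcile 6.4, 7.1, 7.2.1, 7.2.2 and exclusion 9 so that every drug, including one on neither list, has a single status at entry and during the study. Which drugs lead to withdrawal is for the sponsor to decide.
2. State that a patient who meets the 6.4 drug criterion still has the scheduled S7 lipid pair taken (and the S15 pair if in the second phase) where the patient agrees, and is included in the intention-to-treat analysis. The per-protocol set deals with the deviation.

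The cost is a wording amendment. No visit or sample is added beyond those already scheduled. The small downside is that some patients with protocol deviations remain in the intention-to-treat analysis, which the definition in 12.4 already implies.

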#### **6.5. *Approximate duration of the recruitment period depending on the number of patients available***

The recruitment period will have an approximate duration of 6 months.

For reasons of logistics, each participating centre should include a total of between 25 – 60 patients.

## 7. DESCRIPTION OF THE TREATMENT

### 7.1. *Treatment regimens*

During the initial treatment period (8 weeks) the patients will be given either the treatment with *Plantago ovata* husk (Plantaben) or placebo, according to the randomisation group.

The dose will be 20 g p.o. daily in the form of effervescent powder. This is the usual dose of the product in clinical practice.

The product will be distributed into 4 doses of 5 g, taken at main meal times, taking one dose at breakfast time, another at lunchtime and two with the evening meal.

The dose of fibre contained in Plantaben will total 14 g/d.

The duration of the treatment with each product will be 8 weeks. Subsequently, patients that do not fulfil the therapeutic objective will be given an added statin for a further 8 weeks. Patients who reach the therapeutic objective in the first 8 weeks will end follow-up at this time.

The statin chosen is Simvastatin 20 mg/day.

The fibre will be given at least 15 minutes before breakfast, lunch and the evening meal. The contents of the sachet should be dissolved in 200 – 250 ml of water and taken immediately.

The Simvastatin will be taken at night, 2 hours after the evening meal.

If the patient is regularly taking another medication, the time he/she takes it should be checked in order to avoid interference with the taking of the fibre and the statin or both.

If the regular medication is taken in the morning, it will be taken 2 h after breakfast to simulate the situation of fasting. In all cases, the medication should be taken 2 h after the meal.

### 7.2. *Concomitant treatments*

#### 7.2.1. Permitted treatments

- . Diuretics
- . Beta-blockers
- . Calcium channel inhibitors
- . Angiotensin-converting enzyme inhibitors (ACEI).
- . Angiotensin II receptor antagonists (AIIRA).

### 7.2.2 Prohibited treatments

- Statins (during the first 8-week period)
- Resins
- Fibrates
- Nicotinic acid and derivatives
- Ezetimibe
- Anticoagulants
- Minerals and vitamins
- Digoxin

It should be emphasised that patients may have followed some of the prohibited treatments for up to a minimum period of two months before their inclusion in the study.

All the drugs that the volunteer may take must be recorded.

### 7.3. Measures to evaluate compliance

#### Fibre phase

Each participant will be furnished with the fibre treatment, packaged in sachets. Delivery will be at the beginning of the intervention phase (S0) and at the visit after one month (S4). Similarly, at this visit (S4) the participant will return the containers of medication issued at the previous visit (used and unused) and the sachets taken will be counted. If low intake is detected the participant should be warned.

The participant will be given the treatment for the following four weeks at visit S4. At the end of this period (S8), all the containers of medication (used and unused) should be returned to check the sachets taken.

#### Fibre + statin phase

Patients who have to continue with the treatment will be given new medication for 4 weeks, with the statin added. At the week S12 visit each participant will return the medication corresponding to the fibre/placebo and the statin (used and unused) and both will be counted (fibre and statin). If low consumption is detected, the participant should be warned.

The participant will be given the treatment for the following four weeks at this same visit (S12). At the end of the period (S16), all the medication containers (used and unused) will be returned and the number of sachets and tablets taken will be confirmed.

A treatment compliance of higher than 80% will be regarded as suitable.

In view of the importance of diet compliance by the participants throughout the study, a dietician in each centre will be dedicated to the study from the preparation phase.

In order to evaluate diet compliance and detect possible deviations from the defined recommendations, the following procedures will be implemented:

- diet records for 3 days, which will be delivered at the medical visits. (Annex 6)
- Similarly, 24-h diet reminders will be made by phone without notice to guarantee compliance. (Annex 7).
- In order to achieve maximum precision in the calculation of food intake, the volunteers will receive training on how to make measurements at home during the first interview with the dietician. At the following visits by the volunteer to the dietician, the way the usual measures are assessed will be checked.

## **8. TRIAL DEVELOPMENT AND ASSESSMENT OF RESPONSE**

### **8.1. Endpoints**

#### **8.1.1. Primary endpoints:**

The primary endpoint is the reduction of LDL-C, evaluated by the mean of two determinations obtained at the end of the therapeutic intervention with soluble fibre and statins.

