### 4.2. Objectives

#### **Primary endpoint**

To determine the capacity to *reduce by 5% the concentrations of plasma LDL-C* by treatment with soluble fibre –*Plantago ovata* husk– added to a low saturated fat diet in patients with moderate hypercholesterolemia.

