#### **Secondary endpoint**

- To study the combined cholesterol-lowering effect of treatment with *Plantago ovata* husk and statins to achieve the therapeutic objective.
- To analyse the effect of *Plantago ovata* husk fibre on blood pressure.
- To study the effect of the combination of statins with *Plantago ovata* husk on blood pressure.
- To evaluate whether the response on plasma lipids is modulated by the polymorphisms of apolipoprotein E, cholesterol ester transfer protein (CETP), apolipoprotein A-V and FABP 2.
- Furthermore, possible variations of the effects of the soluble fibre and the statins according to the characteristics at the beginning of the study, LDL-C level, gender or BMI will be studied.

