## **8.2. Trial Development**

See Annex 1 and 2

The study design is described schematically below:

- Inclusion period: Week –2 (D–15) , D-10 and D-7 (D-5)
- Randomisation and initiation of the intervention: Week 0 (S0).
- End of the 1st intervention period: Week 8 (S8).
- Beginning of 2nd intervention period (fibre + statin): from week 8 (S8)
- End of the 2nd intervention period: Week 16 (S16)

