### **Visit S8 (Day 56± 3)**

The participants will go to the hospital for a visit addressing the following aspects:

➤ *Clinical*

A clinical history similar to that of S0 will be made

Identify the presence of clinical problems, concomitant treatments, etc.

Collection of adverse events.

Blood pressure and weight will be taken.

➤ *Analytical*

The results of the mean LDL-C value obtained in the two analyses made in the previous week (S7), at most 3 days before visit S8, will be noted. Similarly, the values obtained in the analyses on the last day of S7 will be noted as final parameters of the biochemistry and haematological trial.

➤ *Dietary*

The patients will already have returned the 3-day record the day they went to the hospital for the second blood sample extraction.

The dietician will address the diet follow-up and possible deviations. If the patient has to continue in the study he/she will be given diet guidelines according to his energy needs.

➤ *Medication*

Evaluate compliance with treatment with fibre. The patient should return used and unused medication containers.

**Two situations may arise at this point: 1) The patient has reached the therapeutic objective (LDL-C < 130) and will end the study, or 2) the patient will present an LDL-C ≥ 130 mg/dl and will continue with the same treatment with a statin (Simvastatin) added for a further 8 weeks.**

**The instructions on how to administer the fibre, the Simvastatin and, as the case may be, the patient's regular medication will be gone over once again.**

If the patient is to continue in the trial, the investigator will issue the same medication that the patient was taking + a statin in sufficient quantity for 4 weeks until visit S12.

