### **12.3 Efficacy analysis**

#### **12.3.1 Primary efficacy analysis.**

The primary efficacy analysis will be conducted to evaluate the effect of the treatment with *Plantago ovata* husk versus placebo with regard to plasma LDL-C concentrations in patients with moderate hypercholesterolemia with low saturated fat diet.

The changes in the values of the plasma LDL-C concentrations will be evaluated by creating two endpoints:

- The primary analysis of the primary evaluation will be carried out with the total difference in the concentrations of LDL-C in plasma between visit S8 and visit S0 between both study groups.

- As additional sensitivity measure, the percentage of reduction of the concentrations of LDL-C in plasma between visit S8 and visit S0 between both study groups will also be evaluated.

The principal working hypothesis will be:

$$H_0: \Delta \text{LDL } \textit{plantago ovata} - \Delta \text{LDL placebo} < |7.5| \text{ mg/dl}$$

$$H_1: \Delta \text{LDL } \textit{plantago ovata} - \Delta \text{LDL placebo} \geq |7.5| \text{ mg/dl}$$

Where  $\Delta \text{LDL}$  = final LDL – baseline LDL

The statistical analysis will be carried out using a covariance analysis (ANCOVA) model with the baseline value as co-variable:

$$Y_{it} = \mu + Y_{it\text{BASELINE}} + T_t + e_{it}$$

where,

- |                         |                                                                                                                                              |
|-------------------------|----------------------------------------------------------------------------------------------------------------------------------------------|
| $Y_{it}$                | indicates the value of variable Y (difference in concentrations between visit S8 and visit S0) measured for patient I receiving treatment T. |
| $Y_{it\text{BASELINE}}$ | indicates the baseline value of the variable Y (difference in concentrations between visit S8 and visit S0) measured for patient I.          |
| $\mu$                   | indicates the overall average                                                                                                                |
| $T_t$                   | indicates the fixed effect of the treatment (T = 1 a 2)                                                                                      |

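### Section 8.1.1 places the primary endpoint at the end of fibre plus statin treatment (week 16), which contradicts the fibre-only primary objective in 4.2 and the week-8 primary analysis in 12.3.1

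*Protocol*

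**What the plan says.** Section 8.1.1, the section that defines the primary endpoint, has LDL-C reduction "evaluated by the mean of two determinations obtained at the end of the therapeutic intervention with soluble fibre and statins". Section 8.2 ends the fibre plus statin period at week 16, and the two determinations of week 15 are noted at visit S16.

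Other sections place the primary question earlier:

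- **Section 4.2, primary:** to "reduce by 5% the concentrations of plasma LDL-C" with *Plantago ovata* husk "added to a low saturated fat diet in patients with moderate hypercholesterolemia". No statin is mentioned.
- **Section 4.2, secondary:** the first item is "To study the combined cholesterol-lowering effect of treatment with" husk and statins.
- **Section 12.3.1:** the primary analysis is the "total difference in the concentrations of LDL-C in plasma between visit S8 and visit S0 between both study groups", with the 7.5 mg/dl hypothesis and an ANCOVA. Section 7.2.2 prohibits statins during those eight weeks.
- **Section 12.3.2:** the combination with statins is analysed under the secondary heading.

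The summary gives LDL-C reduction as the primary endpoint without a time point. At visit S8 one of the two possible outcomes is: "The patient has reached the therapeutic objective (LDL-C < 130) and will end the study". Only patients at or above 130 mg/dl go on, with simvastatin added in both arms.

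**The concern.** The section that defines the primary endpoint and the section that analyses it name different time points, different background treatment and different sets of patients. At S8 every randomised patient is due a value and the arms differ only in fibre or placebo. At S16 only the patients who missed the LDL-C goal at S8 are due a value, and all of them are on simvastatin.

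Membership of the week-16 group depends on LDL-C at S8, which is itself the outcome that treatment is meant to change. If fibre works, more fibre patients than placebo patients leave at S8, and those who remain are no longer comparable by randomisation. A primary endpoint defined there would lose the protection of randomisation for the trial's main question.

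The sample size does not settle the matter. Section 6.3 contains one calculation for each time point, and the adopted total of 290 comes from the statin phase.

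**Working it through.** **Inputs, all from section 6.3.** Week 8: difference 7.5 mg/dl, SD 20, 15% losses. Statin phase: difference 7.25 mg/dl (31.4 − 24.15), SD 18.5, allocation 0.85 placebo to 0.75 fibre, 10% losses. Both use α = 0.05 and 80% power. The figures reproduce with a two-sided test, so z₀.₉₇₅ + z₀.₈₀ = 1.960 + 0.842 = 2.802.

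**1. The plan's week-8 figure.** n per group = 2σ²(2.802)²/δ² = 2 × 400 × 7.85/56.25 ≈ 111.6, so 112, as stated. Allowing for losses, 112/0.85 = 131.8, so 132 per group and 264 in total. The protocol states 270, which is slightly more generous.

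**2. The plan's statin-phase figure.** With k = 0.75/0.85 = 0.882, n(placebo) = (1 + 1/k)(σ × 2.802/δ)² = 2.133 × (18.5 × 2.802/7.25)² ≈ 109.0, and n(fibre) = 109.0 × 0.882 ≈ 96.2. Rounded up, these are 110 and 97. The protocol states 111 and 98, within one patient each. Scaling back to randomised patients: 111/0.85/0.90 = 145.1 and 98/0.75/0.90 = 145.2 per arm, hence 145 per group and 290 in total.

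Both calculations reproduce, and 290 belongs to the second.

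**3. Who has no week-16 value.** Section 6.3 expects 75% of fibre and 85% of placebo patients to miss the goal at S8. The rest leave:

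- fibre: 145 × 0.25 = 36.25, about 36
- placebo: 145 × 0.15 = 21.75, about 22

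This is before any other loss and differs by 10 percentage points between arms.

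**4. Power under each reading.**

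| Primary time point | Patients analysed | Power |
|---|---|---|
| Week 8, 15% losses | 145 × 0.85 = 123.25 per arm | 83.7% |
| Week 8, 10% losses | 145 × 0.90 = 130.5 per arm | 85.8% |
| Week 16, as planned | 111 placebo, 98 fibre | 80.7% |
| Week 16, 15% losses | 104.8 placebo, 92.4 fibre | 78.4% |
| Week 16, from 112 per group | 95 placebo, 84 fibre | 74.4% |

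For the first row, SE = 20 × √(2/123.25) = 2.548, and 7.5/2.548 − 1.960 = 0.984, which corresponds to 83.7%.

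Making week 8 primary therefore costs no power at the planned enrolment. The last row shows why the statin phase, and not the week-8 comparison, drives the total to 290.

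**The case against.** The strongest reply is that the intent is clear. Sections 4.2, 12.3.1 and 12.3.2 agree on the fibre-only phase, and 12.3.1 expressly labels S8 minus S0 as the primary analysis. No week-16 comparison between groups is called primary in the analysis section: weeks 8 to 16 get a within-group analysis, and the combination gets a secondary chi-square test. Section 8.1.1 could also be loose wording for the end of each phase, since 8.1.2 goes on to name both phases.

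Much of this stands, and it shows that 8.1.1 is the sentence to change. It does not remove the conflict. The looser reading would give two primary time points, which still disagrees with the single S8 analysis.

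A reader might infer more than the documents support:

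- **That the statin effect of 20–30% quoted in 4.1 would hide a 5% fibre effect.** Both arms receive simvastatin, so a common effect cancels in the difference. Section 6.3 still assumes 7.25 mg/dl between arms, with a smaller SD.
- **That only 209 of 290 patients (98 + 111, or 72%) would be analysable because of the week-16 choice.** That figure also contains the planned 10% loss to follow-up. The part due to the S8 exit rule is 25% and 15% by arm.
- **That week 16 says nothing about fibre against placebo.** Patients continue their assigned product, so it compares the two on top of a statin. The objection is to the selected subset.
- **That two primary tests share one 0.05 and the sponsor may pick between them.** Section 12.3.1 designates one primary analysis. The risk arises only if 8.1.1 is left to stand beside it.

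**Conclusion.** The contradiction holds and should be removed before the plan is relied on. Section 8.1.1 sets a week-16, on-statin primary endpoint, while 4.2, 12.3.1 and 12.3.2 make week 8 on fibre alone primary.

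The consequence of following 8.1.1 literally is a primary comparison among patients selected on LDL-C after randomisation, with about 25% of the fibre arm and 15% of the placebo arm excluded by design. These shares are the protocol's own expectations for missing the goal at S8, applied to 145 per arm before other losses. The actual imbalance will depend on the true effect.

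The two sample size calculations reproduce to within one patient per group, apart from the small allowance in 270, so no sample size error is implied. What 6.3 lacks is a statement of which calculation serves the primary endpoint.

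**What to change.** Three edits to the text:

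1. **Section 8.1.1:** define the primary endpoint as the change in LDL-C from baseline (mean of the D-10 and D-7 determinations) to the end of the fibre-only phase (mean of the two S7 determinations noted at S8), in all randomised patients.
2. **Section 8.1.2:** list the week-16 LDL-C result on fibre or placebo plus statin as a secondary endpoint.
3. **Section 6.3:** state that the primary week-8 comparison needs 112 per group (270 in total with losses, as already given), and that 290 is set by the secondary statin-phase comparison. Add that 145 per arm gives about 84% power at week 8 after 15% losses.

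The blood samples, visits and enrolment target stay as they are, because both pairs of determinations are already scheduled in Annex 1. The cost is a protocol amendment to the wording.
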